**Figure 1 figure1:**
[figure not shown]
Participant ID interpretation of the Vientiane multigenerational birth cohort (VITERBI) participants.

**Figure 2 figure2:**
[figure not shown]
Family tree of the index women of the Vientiane multigenerational birth cohort (VITERBI). DOB: date of birth.

### Ethics Approval

Ethics approval for this study was obtained from the Ethics Commission of Northwestern and Central Switzerland (EKNZ, 2020-00037) and the National Ethic Committee of Health Research, Ministry of Health, Lao PDR (035/NECHR). This research project will be conducted in accordance with the protocol, Declaration of Helsinki [3], Swiss Human Research Act, and Swiss Human Research Ordinance [1] as well as other locally relevant regulations.

### Informed Consent

Eligible participants will be visited initially by study staff. The purpose of this study and its procedures will be explained to participants, and a written informed consent will be obtained. Pregnant women will give consent for themselves and their newborns. For minors (age<18 years), both the pregnant woman and her parents will provide consent. For participants who are illiterate, there will be an additional witness who is not part of the study team. Participation is voluntary, and patients have the right to withdraw from the study at any given point in time with no further obligations. If the participant withdraws at any time, their data will be deleted. Confidentiality of information will be assured to the participants. All participants younger than 18 years are considered vulnerable populations according to the Lao PDR legislation. If the respondent is underage and agrees to participate, he/she needs the authorization of a parent or legal guardian who cosigns the study informed consent.

### Recruitment

We used a variety of sampling methodologies to identify all births between July 1, 2022, and June 30, 2023. To start, we embedded VITERBI recruitment strategies within the existing Laotian health care system. In Lao PDR, public health care services are delivered according to administrative levels, that is, central/national, provincial, district, and village, which operate under the centralized Ministry of Health. We recruited eligible pregnant women from hospitals operating at all 3 levels of care available in Vientiane capital: central/national, district, and village. Health care staff at public health care facilities at the central and district levels facilitate recruitment by notifying VITERBI staff of eligible participants and connecting consenting individuals with VITERBI staff.

VITERBI staff are assigned in teams to 1 of the 4 study districts to conduct recruitment. VITERBI staff partner with local staff working in public health and governance at both the district and village levels through institutional relations formalized by the Lao Tropical and Public Health Institute, a Lao governmental research entity administered by the Lao Ministry of Health. These partnerships involve working closely with key informants such as hospital leadership, health care providers, public administrators, village health volunteers, and local leaders of all administrative levels. Local collaborators generally keep more granular records (eg, unofficial village census) than national partners and maintain situational awareness of their populations’ health status. Key informants from each village within the 4 study districts work alongside VITERBI staff to identify and recruit potential participants. VITERBI staff regularly visit antenatal care clinics known to serve populations that reside in the study districts to recruit eligible women. Enrollment and all data collecting activities of the VITERBI cohort study are coordinated from a central office at the Lao Tropical and Public Health Institute.

Women who were not enrolled during pregnancy are enrolled postpartum to increase enrollment coverage. Birth records are obtained from central hospitals and local health centers to identify recent births that occurred within the cohort window. Staff attempt to contact these women who were neither enrolled nor declined a previous recruitment attempt during pregnancy. Study staff also obtain vaccination records from central health entities to cross-check infant enrollment with both on-time and postpartum recruitment and attempts to recruit women who do not appear in either channel (Figure 3). Access to these records is facilitated by the Lao Tropical and Public Health Institute through the Ministry of Health. Formal birth records obtained from hospitals and vaccination records from the National Immunization Program are used to evaluate recruitment rates. Increasing the overall enrollment coverage of eligible women (prepartum and postpartum) assures that the cohort represents the target population.

Index woman enrollment is the cornerstone for subsequent enrollment of the child’s relatives. In the field, VITERBI staff work closely with the index women to construct family trees detailing relatives of the child who are alive, eligible (living in the 4 study districts), and available to take part in the study. The family tree document guides staff recruitment efforts by providing basic demographic (name, age, and relationship to the child) and contact information of all family members who can be included. As we recruit additional family members, we anticipate their input will continue to guide recruitment and interview of subsequent members by reviewing the family tree document.

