## Discussion

Multigenerational prebirth cohorts provide in-depth information about pregnancy, infants, early childhood, intergenerational health and wealth cycles, and etiology for specific diseases. Conducting longitudinal cohort studies in low-and middle-income countries provides unique challenges that are often not seen in high-income nations.

One key challenge in the specific context of Vientiane capital is the lack of robust information technology systems that would facilitate official data sharing and provide patients with personal records. Although decentralized operations might improve health system equity in hard-to-reach places subject to remote conditions and limited infrastructure, widespread deficiency of interfacility and interagency communication also results in fragmentation of the health system [41]. The VITERBI recruitment methodology employs diverse strategies in an attempt to reach eligible women and their families across different channels of the public health care and municipal systems. Of note, the recruitment efforts of women seeking and receiving care at 2 national facilities, Mother and Child Hospital and the maternity ward of Mahosot Hospital, yielded higher enrollment compared to province-level and district-level facilities. Face-to-face contact with local health staff and officials is an effective strategy for identifying eligible participants, as centralized data sharing and communication are not effective strategies in Lao PDR. Although record-keeping may vary between villages and districts, local staff generally have knowledge and records—both formal and informal—of pregnancies within their jurisdiction. Basing their work out of one of the study districts for prolonged periods, VITERBI staff are able to develop consistent partnerships with local staff at both the district and village levels. This strategy is particularly useful in recruiting women who may not be accessing health services within the previously described VITERBI contact circuit (eg, who are accessing private services or are not accessing any health care services).

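### The recruitment rate is measured only against health-system birth lists, so it cannot support the claim that coverage assures representativeness

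*Protocol article*

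**What the plan says.** The Recruitment section of the protocol article sets the target as every birth in a one-year window: "We used a variety of sampling methodologies to identify all births between July 1, 2022, and June 30, 2023". For women not enrolled in pregnancy, two record sources are used after birth:

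- "Birth records are obtained from central hospitals and local health centers to identify recent births that occurred within the cohort window"
- "Study staff also obtain vaccination records from central health entities to cross-check infant enrollment with both on-time and postpartum recruitment"

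Almost the same sources then serve as the yardstick: "Formal birth records obtained from hospitals and vaccination records from the National Immunization Program are used to evaluate recruitment rates". The only difference in wording is that health-center records are named for finding women but not for evaluating the rate. The next sentence reads: "Increasing the overall enrollment coverage of eligible women (prepartum and postpartum) assures that the cohort represents the target population".

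The section also describes a channel that does not depend on these lists: "Key informants from each village within the 4 study districts work alongside VITERBI staff to identify and recruit potential participants". It mentions unofficial village censuses held by local collaborators, but names no village source for evaluating recruitment. The Discussion says the village-level strategy helps to reach women outside the study's usual contact points, for example those "who are accessing private services or are not accessing any health care services".

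**The concern.** Representativeness of the local population is the first of the three aims. The third aim includes access to antenatal care and adult access to health care. The Statistical Analyses section makes descriptive incidence and prevalence estimates, including use of health care, the main goal.

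The chance that a birth is on a hospital or immunization list depends on contact with the health system, which is close to one of the outcomes to be described. A birth on neither list is missing from the denominator and has no record-based route into the cohort after delivery. Even a rate of 100% would show only that the lists were exhausted. If such a figure were cited as evidence of representativeness, its blind spot would fall on the women whom the access questions most need to include.

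**Working it through.** **Plan's own figure.** There is none to reproduce. The article reports 3500 enrolled pregnant women against a target of 3000 (3500/3000 = 117%). The target is a planned sample size, not a count of eligible births, so this ratio says nothing about coverage.

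**Notation.** All values below are assumptions, because the article gives none.

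- u: share of eligible births on neither list
- pL, pU: probability of enrollment for listed and unlisted births
- w: share of list entries that are ineligible or duplicate

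**Formulas.**

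- True coverage: C = (1 − u)·pL + u·pU
- List-based rate, only enrollees matched to the lists in the numerator: pL·(1 − w). With w = 0 the bias is u·(pL − pU).
- List-based rate, all enrollees in the numerator: C·(1 − w)/(1 − u). With w = 0 this is too high whenever u > 0.

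**Illustration with pL = 0.80, pU = 0.30, w = 0.** For u = 10%: C = 0.90 × 0.80 + 0.10 × 0.30 = 0.75. The matched rate is 0.80, and the all-enrollee rate is 0.75/0.90 = 0.833.

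| u | True coverage | Matched rate (bias) | All-enrollee rate (bias) |
|---|---|---|---|
| 5% | 77.5% | 80.0% (+2.5 points) | 81.6% (+4.1) |
| 10% | 75.0% | 80.0% (+5.0) | 83.3% (+8.3) |
| 20% | 70.0% | 80.0% (+10.0) | 87.5% (+17.5) |

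**How far the result moves.**

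- No unlisted birth enrolled (pU = 0): the matched bias is u × 0.80, that is +4, +8 and +16 points. This is the upper limit for pL = 0.80. It conflicts with the village-informant channel, which can enroll unlisted women.
- Equal enrollment (pU = 0.80): the matched bias is zero.
- Better enrollment of unlisted births (pU = 0.90, u = 20%): C = 0.64 + 0.18 = 0.82, so the matched rate is 2 points too low. The all-enrollee rate is 0.82/0.80 = 102.5%.
- Imperfect lists (u = 10%, pU = 0.30, w = 10%): the matched rate is 0.80 × 0.90 = 72.0% against a true 75.0%, a bias of −3.0 points.

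**Effect on an access outcome.** Assume that 5% of listed and 40% of unlisted women had no antenatal care, with u = 10%. The population figure is 0.90 × 5% + 0.10 × 40% = 8.5%. With pL = 0.80 and pU = 0.30 the cohort would show (0.72 × 5% + 0.03 × 40%)/0.75 = 6.4%, a shortfall of 2.1 points. The matched rate would stand at 80% whatever the value of pU, so it carries no information about this shortfall.

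**A check that is available.** The share of enrollees on neither list is s = u·pU/C. In the three rows of the table this is 0.015/0.775 = 1.9%, 0.03/0.75 = 4.0% and 0.06/0.70 = 8.6%. If unlisted births are enrolled less often than listed ones, s is smaller than u, so it gives a floor for the unlisted share. Failed matches would inflate it.

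**The case against.** The strongest reply has four parts.

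1. **No rate is offered as proof.** The sentence on representativeness concerns overall coverage, including the postpartum route, and does not say that the list-based rate demonstrates it. This stands as a matter of wording. But the two sentences are adjacent, and the lists are the only means named for judging how complete recruitment is.

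2. **Women outside public care are recruited.** Village informants reach them, and the Discussion sentence describes a strategy that works for them. It does not say that they are missing from the cohort. An infant born privately or at home may also appear in immunization records. All of this stands and may make the problem small. It still does not put an unlisted, unenrolled birth into the denominator.

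3. **The lists may err the other way.** The Discussion describes repetitive and poorly organised population data and several names or spellings for one person. Duplicates and failed matches would lower the rate. This stands. It makes the rate harder to interpret, but does not restore the assurance.

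4. **Denominator rules belong in the full protocol.** Agreed. The absence of residence filters or de-duplication rules from a condensed article is not held against it. The point rests on the yardstick and the inference that the article does state.

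A reader might go further and infer that coverage is overstated, or that using the same lists to recruit and to count creates the bias. The documents support neither. Overstatement needs unlisted births that are enrolled less often, or a numerator that counts unlisted enrollees, and neither is documented. Dual use of a list is harmless if the list is complete. What limits the rate is incompleteness of the lists.

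**Conclusion.** The point holds in a limited form. A rate built on hospital birth records and immunization records measures coverage of births known to the health system. It cannot detect non-coverage outside that system, so it cannot carry the statement that coverage assures representativeness. The article itself weakens that statement: it reports higher enrollment through two national facilities than through lower-level ones, and accepts that some routes to eligible women probably remain unused.

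Overstatement is the likely direction if unlisted births are enrolled less often, which is plausible because they lack the record-based postpartum route. Under the illustrative inputs it is 2.5 to 10 points for a matched numerator and 4.1 to 17.5 points if all enrollees are counted. Other inputs give zero or a negative error. The documents fix neither size nor sign.

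**What to change.** - Report the recruitment rate as coverage of births known to the health system, by district, among de-duplicated eligible residents, counting only enrollees matched to the lists.
- Report the share of enrollees who appear on neither list, separately for those found through village informants, as a check on list completeness.
- Where village records can be linked, add a capture-recapture estimate of total births as a sensitivity analysis, with a range for matching error and for dependence between lists. It should not be the main result. Missed matches inflate the estimated total, and women outside all care may be absent from several lists at once.
- Replace the statement that coverage assures representativeness with the coverage result and a statement of who is probably missed.

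**Cost.** The rewording is almost free. The list check needs linkage and analysis work, made harder by handwritten ledgers and inconsistent names. The article does not show that village censuses were collected in linkable form or that each woman's recruitment source was recorded, so the informant breakdown and the sensitivity analysis may not be feasible in every district. The claim of representativeness becomes less favourable.

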Our Vientiane multigenerational birth cohort (VITERBI) is the first multigenerational birth cohort created in the urban and semiurban districts of Vientiane capital, Lao PDR, focused on intergenerational health and life course trajectories of children, their parents, grandparents, and great-grandparents. Cohort data will be analyzed to quantify key health challenges and gaps across population groups, ultimately to develop interventions and social impact programs for the improvement of population health.

VITERBI has 3 main aims:

Establish a multigenerational birth cohort in Vientiane capital, Lao PDR, which is representative of the local population.Serve as the basis for additional observational (ie, cross-sectional) and intervention studies that promote population health in Vientiane province.Investigate the social, epidemiological, and medical problems of public health importance to Lao PDR, including intergenerational prevalence of overnutrition and undernutrition, access to antenatal care, adult access to health care, prevalence and predictors of communicable and noncommunicable diseases within families, the current status of geriatric care, and its socioeconomic determinants.

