## Methods

### Study Design

The VITERBI cohort will be established in the Vientiane capital of Lao PDR and is a prospective longitudinal birth cohort study enrolling children (during pregnancy), their parents, and relatives up to 3 generations (maternal and paternal grandparents and great-grandparents). Four districts of Vientiane capital were purposely selected based on overall socioeconomic status: Chanthabuly and Sikhottabong are 2 districts located in urban areas of high socioeconomic status, while Sangthong and Mayparkngum are 2 districts located in the semiurban, less developed areas of low socioeconomic status.

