### Participants

The target sample size for the VITERBI cohort is 3000 children and their relatives (~13,000) across 4 selected districts. Index women (ie, pregnant women and the first participant enrolled within a family) are eligible for recruitment if they live in Vientiane capital in 1 of the 4 study districts; had an expected due date or gave birth between July 1, 2022, and June 30, 2023; do not plan to permanently move outside the study area; do not have a medical, intellectual, or psychological disability; and agree to participate with a signed informed consent. If the participant is younger than 18 years, a legal representative will additionally need to sign the informed consent. Whenever possible, women will be enrolled during pregnancy; however, women who were not enrolled during pregnancy will be enrolled shortly after birth by using a modified late enrollment questionnaire.

Index women are tracked with a unique VITERBI ID number within the project database. All subsequent family ID numbers retain the number associated with the index woman in addition to their specific unique ID (Figure 1). Thus, all unique personal ID numbers assigned to family members of the child will be associated with the original ID number of the index woman. The ID numbers also indicate the district of residence of the index woman.

Enrollment data from each family member will be used to construct a family tree based around the index woman and child (Figure 2). All enrolled members will be followed up for a minimum of 1 year, with the ambition to extend the follow-up period until 2050. Members of the established cohort will also be recruited and enrolled into additional studies, as they arise.

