## Results

As of April 2024, this study has enrolled 3500 pregnant women and 4579 family members. Study participation is ongoing until May 2025 at minimum, with the goal to extend follow-up until 2050. The cohort has already served as a basis for additional observational and intervention studies that promote population health in Vientiane province: (1) VITERBI GUT, a prospective birth cohort studying the link between early life malnutrition, the microbiota, and metabolic health [5] and (2) a randomized controlled trial providing social transfers to increase exclusive breastfeeding and promote maternal and child health [40].

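### Other than the index women, adults and elders enter only as resident kin of a newborn, so representativeness and the general questions on adult and geriatric care are not supported for them

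*Protocol article*

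**What the plan says.** The Introduction states as first aim a cohort "which is representative of the local population"; the Abstract repeats this. The third aim lists, among other topics, adult access to health care and "the current status of geriatric care, and its socioeconomic determinants".

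The Methods give one route into the cohort. An index woman qualifies if she lives in one of the four districts, "had an expected due date or gave birth between July 1, 2022, and June 30, 2023", and meets the other criteria, such as "do not plan to permanently move outside the study area". Under Recruitment, "Index woman enrollment is the cornerstone for subsequent enrollment of the child’s relatives". Study Design extends enrollment to "relatives up to 3 generations (maternal and paternal grandparents and great-grandparents"), and the notes to Table 1 confirm that the adult questionnaire is for fathers, grandparents and great-grandparents of the child. The family tree drawn up with the index woman lists "relatives of the child who are alive, eligible (living in the 4 study districts), and available to take part in the study". No other route for adults or elders is described.

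Recruitment bases the claim that the cohort represents its target population on coverage of eligible women before and after birth, with recruitment rates checked against birth and vaccination records. Statistical Analyses is narrower than the aims: it speaks of a sample of children and their families.

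**The concern.** Being kin to a newborn is a condition of entry for every adult except the index woman. Adults with no child, grandchild or great-grandchild in the window, or whose young kin live elsewhere, cannot be sampled however well recruitment goes. High coverage of mothers supports statements about mothers and infants. It does not carry over to adults or older people in general.

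At stake is what the cohort may conclude. A prevalence or care estimate among enrolled elders describes elders who live in the four districts and have a newborn descendant there. Read as the status of geriatric care, or as adult access to care in the local population, it answers a different question. The Discussion treats recruitment difficulties at length but does not name this limit. The point is separate from how the four districts were chosen and would remain if they were fully typical.

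**Working it through.** **1. Selection rule against aims.**

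| Element | Where | Who is covered |
|---|---|---|
| Representative cohort | Introduction, aim 1 | Local population |
| Adult access to care; geriatric care | Introduction, aim 3 | Adults and elders, with no family restriction stated for these two items |
| Entry of adults | Study Design, Participants, Recruitment, Table 1 | Index women; fathers, grandparents and great-grandparents who are alive, resident and available |
| Support for representativeness | Recruitment | Eligible women only |
| Main goal | Statistical Analyses | Children and families |

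The third row is a strict subset of the first two. For everyone outside it the selection probability is zero.

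**2. The plan's own figure.** The target of about 13,000 cannot be reproduced, because no number of living, resident relatives per child is given. One child has at most 1 father + 4 grandparents + 8 great-grandparents = 13 such kin, living or dead. Depending on what the 13,000 includes:

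- women and children both included: (13,000 − 6000)/3000 = 2.33 relatives per child, or 2.33/13 = 18%
- women included, children not: (13,000 − 3000)/3000 = 3.33, or 26%
- other relatives only: 13,000/3000 = 4.33, or 33%

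**3. Enrollment reported in Results.** By April 2024 "this study has enrolled 3500 pregnant women and 4579 family members": 4579/3500 = 1.31 per index woman, or 1.31/13 = 10%. If every father had enrolled (an assumption), (4579 − 3500)/3500 = 0.31 grandparents or great-grandparents per index woman. If half had, (4579 − 1750)/3500 = 0.81. These figures mix unfinished recruitment, refusal, death and residence, so they describe how far enrollment had come and do not isolate the eligibility rule.

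**4. What the size could be, on assumed values.** Let f be the share of elders reachable through an index child, p1 the outcome prevalence among them and p0 the prevalence among other elders. Then

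bias = p1 − [f·p1 + (1 − f)·p0] = (1 − f)(p1 − p0).

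None of these inputs is in the documents. With p1 = 10%:

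- f = 5%, p0 = 20%: 0.95 × (−10) = −9.5 points
- f = 30%, p0 = 15%: 0.70 × (−5) = −3.5 points
- p0 = 10%: 0 at any f

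Exchanging p1 and p0 reverses the sign. The illustration shows that bias is possible; it gives neither its size nor its direction here.

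**The case against.** The strongest reply is that a birth cohort built on kin of newborns is the declared design and is partly scoped already. Statistical Analyses refers to children and families, and aim 3 frames nutrition as intergenerational and disease as within families. For those items, families with a birth are the natural target. This stands, and it confines the point to representativeness and to the two general questions. It also shows that the aims are wider than the statistical section. Since the article itself states the aims, the entry rule and the assurance of representativeness, the mismatch is not a detail left to a fuller document.

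A reader might infer more than the documents support:

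- *That only non-migrant families are seen.* The criterion for relatives is residence in the four districts; in-migrants living there can enter.
- *That survivorship distorts the geriatric picture.* Current care concerns living people. Missing dead kin can matter for intergenerational comparisons, where the family survival history in Table 1 helps in part.
- *That elders who die before their own visit vanish.* Recruitment does not say when aliveness is judged relative to that visit.
- *That need for care is understated, or the socioeconomic contrast biased in a known direction.* Nothing in the article fixes a direction. Cognitively impaired or incapacitated elders are not shut out, since a short questionnaire exists for them.
- *That 1.31 relatives per woman measures the loss.* It is an interim count, with participation continuing to at least May 2025.
- *That national estimates are claimed.* Aim 3 speaks of problems important to the country, and the remark about cohorts covering all ages describes what other studies lack.

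**Conclusion.** The point holds as a limit on what may be claimed. Apart from index women, the cohort can describe only living, available fathers, grandparents and great-grandparents, resident in the four districts, of children in the birth window whose mothers are enrolled. For adults and elders in general, neither representativeness nor an answer on access to care or geriatric care follows from the design. This conclusion rests on the stated entry rule alone and needs no assumed number. Questions within families are less affected; there the limit is missing dead or out-of-district kin. The size and direction of any bias are unknown and could be zero.

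**What to change.** In the aims (Introduction, and the matching sentence in the Abstract) and in Recruitment, state that adult and elder estimates refer to kin, living in the four districts, of children born in the window. This brings them into line with Statistical Analyses. Drop or qualify the claim of representativeness for these groups, and reword the items on adult access to care and geriatric care to match.

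Use the family tree to record a status for every father, grandparent and great-grandparent: dead, out of district, unavailable or refused, or enrolled. Report enrollment and results by generation against that denominator. As described, the tree lists kin who can be included, so the other categories may need adding; its figure is not shown and may already hold some of them.

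Do not present weighting as a remedy for elders without a newborn relative: people with zero selection probability cannot be recovered by weights. No source is described either for the wealth of non-enrolled relatives in other households. A general statement on elders would need a separate population-based sample.

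The cost is a narrower claim and added record work. For families already enrolled (3500 index women by April 2024) part of it is retrospective.
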